### **Specific Aim 3: To measure and compare ED operational processes and crowding when targeted and nontargeted rapid HIV screening strategies are fully-integrated into ED care**

**Hypothesis 3:** Enhanced targeted rapid HIV screening is not associated with: **(a)** longer patient waiting times; **(b)** longer patient length of stay times; **(c)** longer patient ED boarding times; **(d)** larger proportion of patients who leave prior to completing medical evaluation; or **(e)** greater overall crowding when compared to traditional targeted rapid HIV screening or nontargeted rapid HIV screening.

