## 4. METHODS

### A. Study Design

#### Specific Aim 1

For this aim, we will perform a multi-center, prospective, randomized, controlled clinical trial to evaluate the effectiveness of three distinct HIV screening approaches. Implementation of a randomized controlled trial will incorporate use of “pragmatic” or effectiveness methodologies, and will allow us to compare

[figure not shown]

the effectiveness of the three screening approaches while minimizing threats to internal validity. Patients will be screened using one of three interventions in a 1:1:1 random sequence; patients will therefore be offered HIV testing based on the results of which screening arm they are assigned, and in the case of the two screening tools, the results of risk assessment. All screening methodologies will be integrated into electronic patient triage systems at each site; as such, the actual randomization process will also be integrated into the electronic system, allowing for real-time concealed random allocation (**Figure 1**). Nurses who perform screening and all ED staff (e.g., physicians, nurses, and technicians) will understand the conceptual goals of the project but will be blinded to the specific hypotheses, and patients will be completely blinded to the purpose of the study.

All of the participating sites have established ED-based HIV testing programs, and all of the testing procedures that occur after patients are identified for HIV testing (i.e., consent for the test, performance of the test, results disclosure, linkage to care, etc.) will have been integrated into clinical processes within each ED as standards of care. The specific interventions being evaluated in this

study relate only to how patients are identified for and offered HIV testing. The standard process used by the DHMC ED and the integration of the three study interventions is described by the “ED Rapid HIV Screening Workflow” figure (**Appendix**).

#### Specific Aims 2 and 3

For these aims, we will perform prospective cohort studies nested in the clinical trial described above.

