## **H. Analytic Plan**

All statistical analyses will be conducted by the Principal Investigator and independently confirmed by the study's biostatistician blinded to study allocation. Final analyses will be performed after cleaning and locking of the dataset. Although no formal interim analyses are planned, the study team may perform preliminary analyses for purposes of presentation at scientific meetings; these instances, if they occur, will be explicitly described as preliminary and qualified as such.

### Specific Aim 1

Descriptive analyses will be performed for all variables. Continuous data will be reported as means with standard deviations (SDs) or medians with interquartile ranges (IQRs), depending on whether they are normally distributed or non-normally distributed, respectively; additionally, categorical data will be reported as proportions or percentages with 95% confidence intervals (CIs). Bivariate statistical tests (e.g., Student's t-test or Wilcoxon rank sum test for two-group parametric or non-parametric comparisons, ANOVA or Kruskal-Wallis test for three-group parametric or non-parametric comparisons, and chi-square test or Fisher's exact test) will be used to compare variables between study groups. Patient-level data will be reported for demographics. Otherwise, patient-visit data will be reported given the relatively large degree of recidivism to EDs; as such, the primary unit of analysis will be patient visits.

All analyses will be performed using the intention-to-treat principle and no interim analyses are planned given the "pragmatic" trial approach and minimal risk to subjects. Given the randomized controlled trial design, the primary comparison will include unadjusted risk ratios (RRs) for newly-identified HIV infection (primary outcome) with 95% CIs, specifically comparing enhanced targeted HIV screening to nontargeted HIV screening (the primary hypothesis of this study). Statistical significance for the primary analysis will be defined as  $<0.05$  based on two-tailed statistical testing, which includes a lower 95% confidence limit of  $>1.0$ .

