Process metric variables for all enrolled patients will be compared between study arms. Because the time and EDWIN or NEDOCs metrics are continuous, they will be reported as means with SDs or medians with IQRs. Bivariate analyses will be used to estimate statistical differences between each process metric and the three HIV screening interventions. Because we propose measuring five ED process metrics, we have defined statistical significance for this part of the analyses to be a Bonferroni-adjusted p-value <0.01. Also, hierarchical multivariable linear regression analyses will also be used to estimate associations between each of the interventions and continuous process metrics, while accounting for clustering at the institution level and adjusting for overall ED crowding as measured by the difference in either EDWIN or NEDOCs for the duration of the patient's visit. If necessary, continuous data will be transformed and multiple imputation will be used in instances where data are missing. The primary unit of analysis will be patient visits.

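### Hypothesis 3 claims that enhanced screening does no operational harm, but the only criterion stated for Aim 3 is a difference test at Bonferroni p<0.01, which cannot support that claim

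*Protocol*

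**What the plan says.** Protocol section 1, Specific Aim 3, words Hypothesis 3 as an absence of harm: "Enhanced targeted rapid HIV screening is not associated with" longer waiting, length-of-stay or boarding times, a larger share of patients leaving early, or "greater overall crowding when compared to traditional targeted rapid HIV screening or nontargeted rapid HIV screening". It therefore has five components and two comparators.

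Section 4.H, Specific Aim 3, sets out the analysis:

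- Tests: "Bivariate analyses will be used to estimate statistical differences between each process metric and the three HIV screening interventions".
- Threshold: "Because we propose measuring five ED process metrics", the protocol continues, "we have defined statistical significance for this part of the analyses to be a Bonferroni-adjusted p-value <0.01".
- Models: "hierarchical multivariable linear regression analyses will also be used to estimate associations between each of the interventions and continuous process metrics". No decision rule is attached to them.

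Section 4.I sizes the trial on new HIV diagnoses only and does not mention Aim 3.

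**The concern.** The hypothesis and the criterion point in opposite directions. A test of difference can reject equality, but failing to reject it does not show that times are not longer. Bonferroni protects against falsely declaring a difference. For a no-harm claim the serious error is falsely declaring none, and moving the threshold from 0.05 to 0.01 makes that error more likely.

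The opposite failure is also possible. Where the sample is very large, a difference too small to matter to anyone could refute the hypothesis. In both cases the conclusion on ED operations would turn on sample size and variance, not on whether the delay is acceptable.

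**Working it through.** **The plan's own figure.** Five metrics at an overall 0.05 give 0.05/5 = 0.01, which matches the stated threshold. The base level and two-sidedness are stated for Aim 1 ("Statistical significance for the primary analysis will be defined as $<0.05$ based on two-tailed statistical testing"). I assume they carry over to Aim 3.

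**What the correction does to a missed harm.** This step needs no SD or sample size. A harm with 80% power at two-sided 0.05 lies 1.960 + 0.842 = 2.802 standard errors from zero. At 0.01 the critical value is 2.576, so power is Φ(2.802 − 2.576) = Φ(0.226) = 0.59. The chance of missing the harm rises from 20% to 41%. A harm with 50% power at 0.05 is missed with probability Φ(2.576 − 1.960) = 0.73 at 0.01.

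**Metrics measured on all visits.** Section 5.C allows up to 120,000 subjects, and section 4.A says "Patients will be screened using one of three interventions in a 1:1:1 random sequence", so there are at most about 40,000 per arm. For a pairwise comparison in SD units, SE = √(2/40,000) = 0.00707.

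- Difference detectable with 80% power: 0.00707 × 2.802 = 0.020 SD at 0.05, and 0.00707 × (2.576 + 0.842) = 0.024 SD at 0.01.
- Smallest observed difference that is significant at 0.01: 0.00707 × 2.576 = 0.0182 SD. The protocol gives no SD. For assumed SDs of 60 to 240 minutes this is 1.1 to 4.4 minutes (3.3 minutes at an SD of 180).
- Leaving before completion, at assumed rates of 3% to 10%: the difference detectable with 80% power moves from 0.34–0.59 to 0.41–0.73 percentage points.

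For these metrics the correction changes little, and a difference of a few minutes is enough to refute the hypothesis.

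**Boarding time.** Section 4.F defines it from the request for an inpatient bed, so only admitted patients contribute. Neither their number nor the SD is given. Two assumed cases show the range:

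| Assumed SD | Admitted per arm | SE = SD × √(2/n) | Largest non-significant excess at 0.05 (1.960 × SE) | At 0.01 (2.576 × SE) |
|---|---|---|---|---|
| 120 min | 10,000 (25%) | 1.70 min | 3.3 min | 4.4 min |
| 300 min | 6,000 (15%) | 5.48 min | 10.7 min | 14.1 min |

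A true 10-minute delay would almost never be missed in the first case: 10/1.70 = 5.9 standard errors, a miss rate below 0.1% at either threshold. In the second case, 10/5.48 = 1.83 standard errors, and it would be missed 55% of the time at 0.05 and 77% at 0.01.

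All of these figures ignore clustering by institution and repeat visits. Enrolment below 120,000 would widen every threshold.

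**The case against.** The strongest reply is that the protocol never says that p>=0.01 confirms Hypothesis 3. It speaks of comparing metrics and estimating associations. That is correct. A reader might infer that the plan declares imprecision to be proof of no harm, and the text does not support that. The reading rests on inference, because no other criterion is given for a numbered hypothesis. If non-significance is not meant to count as support, the plan states no way for the hypothesis to be supported.

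A second reply is that margins and confidence-limit rules for an aim that did not drive the sample size may sit in a statistical analysis plan that is not at hand. This also stands, so the absence of a margin is not itself the finding. The finding is that the protocol fixes a criterion, and that criterion does not suit its own hypothesis.

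Third, the sample is very large. For waiting time, length of stay and leaving early this largely disposes of any practical harm from the 0.01 threshold. A reader might take the 14-minute or 77% figure as typical of Aim 3. It applies to boarding alone, at the less favourable pair of assumed values. Boarding also begins well after triage, so screening may be less likely to affect it.

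**Conclusion.** The point holds in limited form. Hypothesis 3 is a no-harm claim, the only criterion stated for it is a difference threshold, and tightening that threshold to 0.01 raises the chance that a real delay goes undeclared. The 20% to 41% increase, for a harm with 80% power at 0.05, needs no assumption about SD or sample size; it rests on a normal approximation and a two-sided test.

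The practical size depends on the metric. It is mainly logical for the full-sample metrics at about 40,000 visits per arm. It is potentially material for boarding, at roughly 4 to 14 minutes under the assumed SDs and admission numbers. Aim 3 is not the primary aim, and nothing here affects the primary comparison. The wording should be corrected before analysis.

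**What to change.** In section 4.H, Specific Aim 3:

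1. Report the enhanced-minus-comparator difference with a 95% confidence interval for each comparator: the mean difference in minutes for the three time metrics, and the risk difference for leaving before completion. State that p>=0.01 will not be taken as evidence of no association.
2. If a conclusion of not longer or not larger is wanted, set a largest acceptable worsening for each of these four patient-level metrics before the data are analysed. Require the upper limit of the two-sided 95% interval to lie below it, for each comparator. No Bonferroni division is needed if the claim is made only when all these components pass. The protocol does not say whether they stand or fall together, so keep a multiplicity adjustment if they are claimed separately.
3. Report crowding (EDWIN or NEDOCS) descriptively, without a margin. It is an ED-level measure shared by arms randomised concurrently, and its change over the visit is also a covariate in the models.

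The first and third changes cost only wording and use the same data. The second needs agreement on margins. It also needs an analysis that gives a mean or risk difference, because rank tests or transformed outcomes do not directly give an interval in minutes.

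The downside is that the no-harm claim becomes harder to make for imprecise metrics. If the true difference is zero, 90% power requires a margin of (1.960 + 1.282) × SE. That is about 0.023 SD for full-sample metrics, but about 5.5 to 18 minutes for boarding in the two assumed cases, before any allowance for clustering or repeat visits.

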During this aim, we will collect the following data elements for all eligible patients: (1) patient visit information (unique patient identifier, acuity level, mode of arrival, and date/time of visit); (2) demographics (age, sex, race/ethnicity, primary language); (3) payer information (commercial, Medicare, Medicaid, self, or state-sponsored); (4) details of randomization, including the intervention assigned and results of risk screening, if applicable; (5) whether a patient was offered, accepted, and completed rapid HIV testing; (6) results from all rapid HIV tests; and for all patients with at least one reactive HIV test; (7) results of confirmatory test results, additional behavioral risk information as collected during post-test counseling, initial CD4 counts and viral loads, whether they were successfully linked into care, and details of follow-up care and disease progression. Data from (1) through (5) will be collected prospectively using methods developed and validated in Denver from each institution's electronic screening, patient tracking, and laboratory reporting systems. Our study team has extensive experience interfacing with such systems and obtaining large amounts of valid patient-level data. Data from (6) and (7) will be retrospectively obtained using trained personnel and structured procedures. See **Data Dictionary, "Positive Patient Risk Information Data Collection Instrument"** and **"Longitudinal Data Collection Instrument" / "Limited Longitudinal Data Collection Instrument"** in the **Appendix**.

Specific Aim 2

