In this aim, we will collect additional ED process data in conjunction with patient enrollment as part of the clinical trial described in Specific Aim 1. We will include data from all patients enrolled in Specific Aim 1. Values for each of the four basic time metrics (patient waiting time, patient length of stay, patient boarding time, and proportion of patients who leave before completion of evaluation) will be collected real-time for all enrolled patients evaluated in each ED using electronic patient tracking systems. Patients who register for evaluation in each ED on a daily basis include time stamps related to initiation of medical screening, ED bed assignment, patient discharge or admission to the hospital and, if admitted to the hospital, inpatient bed assignment. The fifth metric, ED crowding, will be calculated using one of two validated ED crowding metrics (described in detail below). See **Data Dictionary** in the **Appendix**.

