where 0 – 20 is considered “not busy”, 21 – 60 considered “busy”, 61 – 100 considered “very busy”, 101 – 140 considered “crowded”, 141 – 180 considered “dangerous”, and 181 or greater considered “disaster”. EDWIN and NEDOCS have been compared head-to-head and have both been shown to be valid and comparable metrics for quantifying ED crowding.

Values for each of the four basic time metrics will be collected real-time for all patients enrolled into the study using electronic patient tracking systems. Patients who register for evaluation in each ED on a daily basis include time stamps related to initiation of medical screening, ED bed assignment, patient discharge or admission to the hospital and, if admitted to the hospital, inpatient bed assignment. Because EDWIN and NEDOCS rely on point-in-time sampling and at the level of the ED, it is not feasible to measure their variables on a continuous, real-time basis. However, we will calculate the fifth ED metric, either EDWIN or NEDOCS, at the time each patient begins medical screening and when he or she is discharged. The difference between these data will be used as a covariate in the analyses for this aim as described below.

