Secondary comparisons will include unadjusted RRs for: (1) traditional targeted HIV screening to nontargeted HIV screening (the secondary hypothesis of this aim); and (2) the composite secondary outcome, newly-diagnosed and repeat-diagnosed HIV infection for both hypotheses. Additionally, HIV prevalence, including overall prevalence and test prevalence, and 95% CIs will be reported for each study group, and institution-specific subgroup analyses will be performed as well as hierarchical multivariable binary Poisson regression to account for clustering at the level of the institution and repeat visits at the level of the patient, while adjusting for age, sex, race/ethnicity, primary language, pay status, and acuity level. Results of these latter analyses will be reported as adjusted RRs with 95% CIs. Finally, additional comparative analyses will be performed, including: (1) absolute numbers of new HIV diagnoses; (2) proportions identified early in the disease course (defined by an initial CD4  $>350$  cells/ $\mu$ L) and late in the disease course (defined by an initial CD4  $<200$  cells/ $\mu$ L); (3) proportions successfully linked into care; (4) patient characteristics stratified by those who do and do not agree to HIV testing after screening; and (5) frequency of unscheduled medical visits, use of antiretroviral therapy, treatment for opportunistic infections, hospitalizations, and mortality over the 12 months following initial diagnosis. Any other analyses will be considered exploratory and described as post-hoc.

### Specific Aim 2

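### The Aim 3 regression could gain a little precision, at almost no cost, by adding baseline covariates that the trial already collects

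*Protocol*

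**What the plan says.** Section 4.H (Analytic Plan, Specific Aim 3) first compares each process metric across the three arms with bivariate tests. It sets the threshold: "we have defined statistical significance for this part of the analyses to be a Bonferroni-adjusted p-value <0.01". It then adds a hierarchical linear regression of the continuous metrics on intervention, "while accounting for clustering at the institution level and adjusting for overall ED crowding as measured by the difference in either EDWIN or NEDOCs" over the visit. No patient-level baseline variable is named. Section 4.F explains that crowding is calculated "at the time each patient begins medical screening and when he or she is discharged", and that the difference between the two values is the covariate.

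The baseline data exist. Section 4.E (Specific Aim 1) lists, for all eligible patients, visit information ("unique patient identifier, acuity level, mode of arrival, and date/time of visit") and demographics including age. Section 4.E (Specific Aim 3) links the two aims: "We will include data from all patients enrolled in Specific Aim 1".

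The adjusted model for Aim 1, also in section 4.H, does use patient-level variables, "adjusting for age, sex, race/ethnicity, primary language, pay status, and acuity level". The protocol gives no reason why the Aim 3 model has none.

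**The concern.** Hypothesis 3 says that enhanced targeted screening is not associated with longer waiting, length-of-stay or boarding times. A claim of no delay is only as informative as its confidence intervals are narrow. Acuity, arrival mode, age, and hour and day of arrival are plausible predictors of how long a visit takes, and they describe the patient or the arrival rather than the screening method. Adjusting a randomised comparison for such variables removes between-visit variation from the error term.

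The protocol names an adjustment set for this regression, so this is not simply detail left for later, and the set uses none of these variables. What is at stake is some avoidable width in the regression intervals for the three time metrics. It is most visible for boarding time, which exists only for admitted patients and so has the fewest observations.

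**Working it through.** **Inputs from the protocol**
- Up to 30,000 subjects at each of four sites (section 5.C): 4 × 30,000 = 120,000. Allocation is 1:1:1 (section 4.D), so there are up to 120,000 / 3 = 40,000 visits per arm.
- Aim 3 threshold of 0.01 for five metrics (section 4.H). Check: 0.05 / 5 = 0.01, which reproduces the stated figure. The matching interval is 99%, with z = 2.576.

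**Assumptions (the protocol gives no SD, variance explained, admission rate, margin or power for Aim 3)**
- The added covariates explain a share R² of the variance left after the stated adjustment, with R² from 0.10 to 0.30.
- Length of stay: SD 200 minutes. Boarding time: SD 240 minutes, with 20% of visits admitted, so 0.20 × 40,000 = 8,000 per arm.
- Times are analysed untransformed, and repeat visits by one patient are ignored.

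**Formulas**
- Half-width of the difference between two arms = 2.576 × SD × √(2/n) × √(1 − R²).
- Equivalent gain in visits = 1/(1 − R²) − 1.

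**Relative gain**
- R² = 0.10: √0.90 = 0.949, so intervals are 5% narrower, equivalent to 11% more visits.
- R² = 0.30: √0.70 = 0.837, so intervals are 16% narrower, equivalent to 43% more visits.

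A 400-run simulation with four sites, the crowding covariate retained, and acuity and hour added gave a standard-error ratio of 0.886, against 0.887 from the formula.

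**Absolute gain at the 0.01 threshold**

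| Metric | n per arm | Stated model | R² = 0.10 | R² = 0.30 |
|---|---|---|---|---|
| Length of stay, SD 200 min | 40,000 | 2.576 × 200 × √(2/40,000) = 3.6 min | 3.5 min | 3.0 min |
| Boarding time, SD 240 min | 8,000 | 2.576 × 240 × √(2/8,000) = 9.8 min | 9.3 min | 8.2 min |

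**If enrolment is smaller.** The 40,000 is an upper figure, because enrolment stops at 14,000 tests. Section 4.I assumes 25% test completion in the nontargeted arm and 5% in the enhanced arm. If the traditional arm completes between 5% and 25% (assumed), visits per arm lie between 14,000 / 0.35 = 40,000 and 14,000 / 0.55 ≈ 25,500. At 25,500 the half-widths under the stated model are about 4.6 minutes for length of stay and 12.3 minutes for boarding. The proportional gain is the same.

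**The case against.** The strongest reply is that nothing here is wrong. Arms are compared by randomisation, so leaving out baseline covariates does not bias the comparison. The regression is an additional analysis after the bivariate tests, and covariates do not alter those tests. At up to 40,000 visits per arm, the 99% half-width is already about 0.018 SD. With no delay margin in the protocol, nothing shows that a fraction of a minute would change a conclusion. The protocol does not call its covariate list exhaustive, and an analysis plan that is not shown here could add to it. All of this stands, and it limits the point to a minor one.

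Three further cautions also stand. The crowding term may already absorb part of any hour or day effect, which would lower R². Section 5.A says that randomisation happens automatically during triage, and no section says that acuity is recorded first. The added variables may have missing values.

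A reader might infer more than the protocol supports:
- **That the omission biases the no-delay comparison, or widens every Aim 3 interval.** It does neither. The gain is confined to the regression for the three time metrics. Leaving before completion is a proportion outside the linear model, and patient-level covariates are unlikely to help much with the department-level crowding score.
- **That these variables largely determine visit length.** The protocol gives no figure for this.
- **That the crowding term should go, or that institution should become a fixed effect.** Neither follows from an argument about precision.

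The reply does not remove the point itself. The protocol names a covariate set for this model, the set contains no patient-level baseline variable, and the data are already in hand.

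**Conclusion.** The point holds as a minor, nearly free improvement. With R² of 10-30%, the regression intervals narrow by 5-16%. That is about 0.2 to 0.6 minutes off the half-width for length of stay (3.6 to 3.5-3.0) and about 0.5 to 1.6 minutes for boarding time (9.8 to 9.3-8.2). These figures rest on assumed R², SDs and admission rate, and on the upper enrolment figure. They will be smaller if the crowding term already captures time-of-day variation.

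Precision is not the main limit on the Aim 3 conclusion. The validity of the arm comparison is not in doubt on this ground.

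**What to change.** In section 4.H, Specific Aim 3, add acuity level, mode of arrival, age, hour of day and day of week of arrival to the stated hierarchical regression for waiting time, length of stay and boarding time. Keep the planned accounting for institution. Decide separately whether the crowding-change term stays. State that acuity is the value assigned at triage, and confirm that it is recorded before, or without regard to, the assigned screening arm. Make the change before the final analysis.

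The cost is a sentence or two in the plan and a slightly longer model. No new data are needed. Missing covariate values can be handled by the multiple imputation already planned for this aim.
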